# Art-Based Intervention to Promote Psychological Adjustment, Self-Concept, and Quality of Life in Children: Protocol for a Cluster Nonrandomized Controlled Trial

**DOI:** 10.2196/84994

**Published:** 2026-08-12

**Keywords:** cost-effectiveness, emotional adjustment, quality of life, child health, community galleries, self-concept

## Abstract

**Background:**

Children’s mental health is a critical public health priority, with approximately 8% of children aged 10 years or younger experiencing mental, behavioral, or emotional disorders. Despite evidence supporting early intervention, access to mental health services remains limited, particularly for socioeconomically disadvantaged populations. Art-based interventions have emerged as promising approaches to support mental health and socioemotional development. However, significant gaps persist in understanding their efficacy, scalability, and long-term impact.

**Objective:**

This study aims to evaluate the effectiveness and cost-effectiveness of a community-based visual arts intervention on children’s self-concept, psychological adjustment, and health-related quality of life (HRQoL) in vulnerable communities.

**Methods:**

This study is a cluster nonrandomized controlled trial with children from socioeconomically disadvantaged neighborhoods. Children aged 6 to 12 years (n=156; intervention: n=104, 66.7%; waitlist control: n=52, 33.3%) will be recruited through schools and community projects. Allocation to the intervention or waitlist control group will be based on neighborhood or cluster membership. The intervention consists of 1-hour weekly visual arts sessions over 9 months led by a professional artist, culminating in community art exhibitions. Assessments will be conducted at baseline (T1) and postintervention assessment (T2) using validated measures: the Strengths and Difficulties Questionnaire (SDQ) for psychological adjustment, the Self-Perception Profile for Children (SPPC) for self-concept, and the Child Health Utility 9D (CHU9D) for HRQoL, as well as societal resource use and related costs. Quantitative data will be analyzed using regression models and intention-to-treat principles.

**Results:**

This study was funded in September 2023. Recruitment began in March 2024 and ended in July 2025. As of April 2024, a total of 179 participants had been enrolled. Data collection was completed in July 2025, and analysis is expected to begin in April 2026. Results are anticipated to be published in September 2026.

**Conclusions:**

This project has the potential to enhance children’s self-concept, psychological adjustment, and HRQoL through participation in a community-based visual arts intervention. The study design, with assessments at preintervention and postintervention time points, will provide valuable insights into the trajectories of psychosocial and quality-of-life outcomes in this population. In addition, the combination of psychosocial assessment and economic evaluation will generate important evidence on the cost-effectiveness of art-based interventions, informing both educational and public health decision-making.

**Trial Registration:**

ClinicalTrials.gov NCT07165704; https://clinicaltrials.gov/study/NCT07165704

**International Registered Report Identifier (IRRID):**

DERR1-10.2196/84994

## Introduction

### Background

Children’s mental health has been recognized as a critical public health priority, with the latest reports showing that approximately 8% of children younger than 10 years experience mental, behavioral, or emotional disorders [1]. Most children never seek nor receive adequate treatment at a sufficiently early age [2], causing a significant negative impact on familial, peer, and academic functioning, worsening comorbid conditions, and lowering quality of life [3,4]. Mental health problems are common and frequently emerge early in childhood with the potential for lifelong impact [5,6]. Childhood is a sensitive period because the developing brain is more susceptible, making mental health care and support most successful when received early [1]. Thus, even in high-income countries, children often face challenges in accessing mental health services, which tend to be inconsistently available and vary in quality [4].

To address these issues, several conventional methods have been used to promote children’s mental health and prevent mental illness, such as school and community-based interventions [7,8], digital health–based interventions [9], and physical activity interventions [10]. Additionally, one promising approach is the use of the arts as a tool [11,12]. A growing body of research has explored the impact of art-based interventions on both physical and mental health, well-being, and quality of life across the lifespan. Research indicates that participating in art activities can promote various outcomes, such as heightened social interaction, improved emotional regulation, reduced mental distress, and better socioemotional growth [11,13-17]. One possible explanation is that art-based interventions enhance a person’s ability for creative thought and action [18], facilitate nonverbal communication, promote self-expression, and foster social connectedness, which may contribute to alleviating emotional problems [19], enhancing self-esteem [20] and self-concept [21], and improving psychological adjustment [22-24].

Despite the promising findings, significant gaps remain in understanding the efficacy of art-based mental health interventions. A primary limitation is the small sample sizes commonly used in studies, which restrict the generalizability of findings and hinder the ability to establish causality [25]. Additionally, there is limited evidence regarding the scalability and long-term efficacy of such interventions, which constrains their broader implementation and impact [11]. Furthermore, little is known about the specific impact of specific visual arts interventions on socioeconomically disadvantaged populations, particularly children [26]. These disadvantaged groups seem to face particular challenges, such as low income, high prevalence of parent’s mental health problems, low education, and are more likely to experience adversity and related life events (RLE) [1].

### Study Setting

The present study is set in Porto, the second-largest city in Portugal, and targets children living in socioeconomically disadvantaged neighborhoods. According to Statistics Portugal, a significant proportion of children live below the poverty threshold, with higher concentrations in metropolitan areas such as Porto [27]. Portugal’s mental health care system has an insufficient availability of community services, particularly affecting children and youth [28,29]. Epidemiological studies on the diagnosis, prevalence, and access to mental health services for children and adolescents are scarce in Portugal, and there is a recognized need to integrate schools and community-based programs into mental health care to improve access [29-31].

Addressing these gaps is essential to advance the understanding of how art-based interventions can support mental health, particularly in vulnerable populations. Therefore, this study seeks to address these gaps by using a longitudinal approach to investigate the impact of art-based interventions on children from vulnerable populations, focusing on their socioemotional development and psychological adjustment.

### Study Aims

This study aims to evaluate the potential benefits of an art-based intervention in improving children’s self-concept, psychological adjustment, and health-related quality of life (HRQoL). Specifically, the primary objective is to assess the impact of the intervention on children’s psychological adjustment, and the secondary objectives are to assess the effect of the intervention on children’s self-concept and HRQoL and to investigate the cost-effectiveness of the intervention compared with a waitlist control. By addressing these aims, the study will provide evidence on the effectiveness and cost-effectiveness of an art-based intervention as a tool for promoting mental health and social integration among children in disadvantaged settings.

## Methods

### Design

The study design is a cluster nonrandomized controlled study with 2 arms: the intervention group, which includes neighborhoods participating in different activities, and a waitlist control group, which includes neighborhoods starting the intervention in year 2. The nonrandomized design was adopted because of ethical and structural constraints inherent to the community-based setting. Clusters were preexisting and defined by schools and community projects located in distinct neighborhoods. Because the participating institutions were already organized as groups, students or participants could not be redistributed or reorganized for randomization purposes. Individual randomization was also not feasible, as the intervention was delivered in a group format within each institution, that is, to a class or group simultaneously. Data collection ran from March 2024 to July 2025, and data cleaning and analysis started in April 2026.

### Participants

The target population will be children aged 6 to 12 years. To be eligible for the study, children must be enrolled in primary school and attending one of the 10 project institutions or partner schools and residing in socially deprived neighborhoods in Porto identified as being at risk of social exclusion. Children with a cognitive deficit, a neurological disorder, or a global developmental disorder will not be eligible.

On the basis of an expected medium effect size (Cohen *d*=0.5), an α error probability of .05, and 90% statistical power, using the difference of means between 2 independent samples with a 2:1 allocation ratio, we estimate that a total of 156 participants will be required to detect significant results (n=104, 66.7% in the experimental group and n=52, 33.3% in the control group). We anticipate fewer participants in the control group at the end of the study due to its higher likelihood of dropout [32]. Participants in the control group are not directly involved in the intervention, which may decrease their perceived benefit, reduce their engagement, and increase the possibility of withdrawal compared with those actively participating in the experimental intervention. However, if this occurs, the results will not necessarily be biased [33]. This consideration justifies the use of a 2:1 allocation ratio, ensuring sufficient statistical power despite the potential for unequal group retention rates. To account for an estimated 30% dropout or refusal rate, we will initially recruit approximately 223 participants.

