### The Art Intervention Community Galleries

The art intervention will consist of 2 parts. First, implementation of a 1-hour visual arts session (eg, painting, drawing, and printing techniques exercises) once a week for 9 months with the experimental group. Sessions are delivered in person, in real time, in a group format of 10 to 20 children per venue, across 10 community venues situated in socially deprived neighborhoods of Porto. The activities will be guided by a theme (emotions) by a qualified art facilitator (artist) with prior experience working with children to obtain a final individual artistic product. The session structure is adaptive: while the thematic focus and the artistic medium remain consistent, the facilitator adjusts pacing, complexity, and sequencing in response to participants’ receptivity and motor and cognitive capacities, given that children range in age. Each session typically includes (1) an introductory phase in which the facilitator introduces the theme and demonstrates a technique using materials such as paints, watercolors, pencils, canvas, paper, and accessible printmaking plates; (2) an active creation phase in which participants produce individual artwork independently within the group setting; and (3) an informal sharing phase in which children exchange ideas, difficulties, and improvements with peers. Through strategies such as repetition, observation, and imagination, the exercise promotes a spirit of inquiry and learning. Peer contact, shared learning, and a feeling of community are all made possible by the group-based approach. The facilitator will provide support, motivation, and technical training while guiding participants through the creative process and will also monitor adherence by collecting signatures to confirm attendance at the sessions. Using narrative-building and dialogue-based methods, the artist will encourage children to share their stories, experiences, and perspectives through art. Narrative-based techniques use narrative to investigate human experiences, emotions, and perspectives. By constructing tales via art, individuals may make sense of their experiences, manage complicated emotions, and get a better understanding of themselves. Dialogue-based strategies enable people to have meaningful conversations about their experiences. The intervention is guided by several interrelated principles. Self-expression is a foundational orientation, with participants afforded autonomy to represent their emotions and experiences according to their own visual preferences within a technically guided framework. Individual self-worth is promoted through the public display of artwork in community exhibitions. Emotional exploration constitutes the thematic spine of the program, providing a coherent and recurring psychological framework across all sessions. The session design also promotes present-moment engagement through attentive sensory involvement with materials, including awareness of hand movements, textures, and visual composition, as well as aesthetic appreciation of color, form, and harmony. Creativity and personal narrative are central to the activity design, and the group format fosters a sense of belonging and shared identity. The intervention is expected to promote emotional regulation through sustained engagement with emotion-focused creative tasks, self-concept through the experience of competence and the valorization of each child’s artistic production, relational security through the consistency of the same facilitator throughout the project and the stable composition of preexisting peer groups, and group cohesion and agency through collaborative sharing, peer learning, and guided autonomous creative choice-making.

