#### Mixed-Effects Model Analysis

Data analysis will follow the intention-to-treat and per-protocol principles and the Standard Protocol Items: Recommendations for Interventional Trials (SPIRIT) statement guidelines for reporting and analyzing trials [57]. The confirmatory analysis of the primary end points (psychological adjustment, self-concept, and quality of life) will use mixed-effect regression modeling (hierarchical linear multilevel models) that accounts for the longitudinal structure and adjusts for potential confounders. The response variables will be the total scores and subscales of measures assessing conduct problems and self-concept, while the interaction terms between time and groups will represent the adjusted effects of the visual arts intervention and will be presented as the main study findings (hierarchical comparisons of treatment conditions with the control group). The models will also include a random intercept for the cluster to account for the nested structure of the data.

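### The 90% power for 156 children comes from a calculation on independent children, with no allowance for the roughly 10 intact clusters that are allocated

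*Protocol article*

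**What the plan says.** The Participants section takes a standardised effect of 0.5, α of .05 and power of 90%. It describes the method as "using the difference of means between 2 independent samples with a 2:1 allocation ratio". The result is 156 children, 104 and 52. The section does not say whether the test is one- or two-sided. The only inflation is for 30% dropout or refusal, to about 223. The same section argues that the 2:1 ratio keeps power adequate if retention differs between arms.

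The rest of the protocol describes a cluster design. Under Design: "Clusters were preexisting and defined by schools and community projects located in distinct neighborhoods". The Abstract assigns arms by neighborhood or cluster membership. The Participants and Procedures sections give 10 institutions and 10 neighborhoods. The intervention section has sessions delivered "in a group format of 10 to 20 children per venue, across 10 community venues". Procedures has teachers or project technicians, depending on the cluster, rate the children on the primary outcome. The Mixed-Effects Model Analysis section allows for nesting: "The models will also include a random intercept for the cluster".

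**The concern.** The analysis recognises that children in the same school or project resemble one another; the sample size does not. When whole clusters are assigned, the variance of the arm difference grows with the ICC and the cluster size, and with about 10 clusters the comparison has few degrees of freedom. A formula for independent children leaves out both.

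What is at stake is how the result is read. If 90% stands unqualified, a null finding may be taken as good evidence against a medium effect, when the real chance of detecting one could be much lower. The figure is fixed in the protocol with its method, inputs and answer, so this is not a detail left to the analysis plan.

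**Working it through.** **Inputs from the protocol.** d = 0.5 (SD = 1), α = .05, power 90%, 104 + 52 children, 30% loss, about 10 clusters, groups of 10 to 20. The mean size 156/10 = 15.6 fits that range.

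**Assumptions (not in the protocol).** Cluster split 7:3; ICC 0.01, 0.02, 0.05, 0.10; pre-post correlation r where used.

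**Step 1: reproduce 156.** Controls needed = 1.5 × (z for α + z for power)² / d².
- One-sided: 1.5 × (1.645 + 1.282)² / 0.25 = 51.4, so 52 controls and 156 in total. This matches.
- Two-sided: 1.5 × (1.960 + 1.282)² / 0.25 = 63.1, so 64 controls and 192 in total. This does not match.
- Loss: 156 / 0.70 = 222.9, so 223. This matches.

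No room is left for a clustering allowance. By noncentral t with 154 df, 104 + 52 children give 90.1% one-sided and 83.3% two-sided.

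**Step 2: add the design effect.** Variance of the difference = [1 + (m1 − 1) × ICC]/104 + [1 + (m2 − 1) × ICC]/52, with m1 = 104/7 = 14.86 and m2 = 52/3 = 17.33. The noncentrality is 0.5/√variance. Example at ICC 0.05: 1.693/104 + 1.817/52 = 0.0512, noncentrality 2.21; without clustering they are 0.0288 and 2.94.

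**Step 3: small-cluster degrees of freedom.** Use t with 10 − 2 = 8 df.

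**Step 4: baseline adjustment.** Multiply the variance by 1 − r²; at r = 0.6 this is 0.64.

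| ICC | One-sided, 154 df | Two-sided, 154 df | Two-sided, 8 df | Two-sided, 8 df, r = 0.6 |
|---|---|---|---|---|
| 0 | 90.1% | 83.3% | 73.2% | 89.5% |
| 0.01 | 86.0% | 77.7% | 67.1% | 84.9% |
| 0.02 | 82.0% | 72.4% | 61.7% | 80.3% |
| 0.05 | 71.0% | 59.3% | 49.3% | 67.8% |
| 0.10 | 57.5% | 44.9% | 36.9% | 52.6% |

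**Sensitivity.**
- A 6:4 split changes the two-sided 8-df column little: about 68, 63, 52 and 40% for ICC 0.01 to 0.10.
- A plain change-score analysis at r = 0.6 has variance factor 2(1 − 0.6) = 0.8 and gives 76.5, 71.3, 58.3 and 44.2% (two-sided, 8 df).
- At r = 0.6, one-sided with 8 df: 92.9, 90.0, 80.9 and 67.7%.
- At r = 0.7 (factor 0.51), two-sided with 8 df: 91.7, 88.2, 77.3 and 62.0%.

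So 90% can be reached, but only with a favourable mix of low ICC, high pre-post correlation and one-sided testing; not all three are needed together.

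**Splitting one fall into its parts.** From 90.1% one-sided to 67.1% (two-sided, 8 df, ICC 0.01): sidedness 90.1 to 83.3 (about 7 points), 8 df 83.3 to 73.2 (about 10), design effect 73.2 to 67.1 (about 6). The split depends on the order taken, but it shows that the design effect is only part of the fall.

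**The case against.** Nobody can point to a clustering allowance elsewhere; the 30% covers dropout or refusal only. The case on the other side concerns how much follows.

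- **Attribution.** Setting the two-sided, 8-df figures against 90% charges clustering with losses that come from sidedness and the degrees-of-freedom convention. This stands, so the parts are shown separately above.
- **The planned estimand.** The main result is the group-by-time interaction. A stable cluster effect cancels from pre-post change, so the ICC that matters is that of change, which may be lower or higher than the cross-sectional one. This stands too. It calls for an ICC stated for the quantity analysed; it does not make zero a safe default.
- **Cluster inputs.** The split by arm is not given, and delivery to a class or group leaves open several groups per institution, so 8 df is an approximation. Nor does the protocol say that a single rater scores each whole cluster. Shared raters could raise the within-cluster correlation, but that is inference.
- **Consequences.** A reader might infer that the Discussion's statement about using a larger sample than earlier studies rests on the 90%. It does not: it compares sample sizes and makes no power claim. A null result can also be read from its confidence interval.
- **Timing.** Data collection ended in July 2025 and the model already has a cluster term, so correcting the power statement changes no estimate. That limits the cost of the error; it does not make the figure right.

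**Conclusion.** The point holds as a statement about the calculation: 90% for 156 children is an individual-level, one-sided figure, and it does not carry over to a trial that allocates about 10 intact clusters. Without baseline adjustment, power is below 90% at every ICC examined, from about 86% (one-sided, ICC 0.01, design effect only) down to about 37% (two-sided, ICC 0.10, 8 df). With r = 0.6 the two-sided 8-df range is about 85% to 53%.

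A reader might go further and conclude that the trial cannot have 90% power. The protocol does not support that. It gives no ICC, split by arm, pre-post correlation or sidedness, and some plausible combinations do reach 90%. What is established is that the stated calculation does not show it. All figures after the first step rest on the assumed split, ICCs and correlations.

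**What to change.** Replace the independent-samples statement in the Participants section with a cluster calculation that gives:

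- whether the test is one- or two-sided;
- clusters per arm and mean cluster size;
- an ICC range, for example 0.01 to 0.10, saying whether it applies to the outcome or its change;
- the resulting design effect and the small-cluster degrees of freedom;
- any pre-post correlation assumed for baseline adjustment.

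Report power or the detectable effect as a conditional range, both for 156 children and for the achieved sample (the Results section gives only 179 enrolled, dated April 2024). Withdraw the unqualified 90%.

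No extra recruitment is needed. The cost is a recalculation, a rewritten paragraph and a less favourable stated figure.

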## Discussion

### Anticipated Findings

This protocol describes a cluster nonrandomized controlled trial to assess a community-based visual arts intervention for children. We hypothesize that participating in a visual arts intervention will be associated with improvements in psychological adjustment, self-concept, and HRQoL compared with a waitlist control group. A cost-effectiveness analysis will also be conducted to estimate the cost per QALY gained. By encompassing the psychosocial and economic domains together, this study can make an important contribution to the evidence base on art-based intervention for children’s psychological adjustment and self-concept. The findings could inform scalable, low-cost, and culturally adaptable strategies for promoting better outcomes for children in disadvantaged settings. If successful, the Community Galleries—Art and Children in Action approach could be extended on a broader scale as part of educational and public health policies.

Previous studies have been characterized by small sample sizes, short intervention periods, and methodological designs that limit generalization and causal inference [11,25]. Furthermore, little is known about the specific impact of community-based visual arts interventions on children’s mental health, specifically in socioeconomically vulnerable contexts [26]. In addition, economic evaluations remain scarce in this field [50]. Our study will address these gaps by using a waitlist control group for comparison, a larger sample, an intervention period of 9 months, validated and standardized outcome measures, and the inclusion of a cost-utility analysis. We also aim to prioritize ecological validity by implementing the intervention in natural school contexts, which will enhance the transferability of findings to real-world contexts.

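### The sample size of 156 assumes an undeclared one-sided α of .05; under a two-sided test its power is about 83%, not 90%

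*Protocol article*

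**What the plan says.** The Participants section gives every input but one. The effect size is a conventional medium value ("On the basis of an expected medium effect size (Cohen *d*=0.5"), the error rates are "an α error probability of .05, and 90% statistical power", and the method is stated as "using the difference of means between 2 independent samples with a 2:1 allocation ratio". The result is "we estimate that a total of 156 participants will be required to detect significant results", split as "n=104, 66.7% in the experimental group and n=52, 33.3% in the control group". The allowance for loss follows: "To account for an estimated 30% dropout or refusal rate, we will initially recruit approximately 223 participants". The Methods paragraph of the abstract repeats the target ("n=156; intervention: n=104, 66.7%; waitlist control: n=52, 33.3").

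The missing input is the number of sides. Neither the sample size paragraph nor the abstract gives it. The section on mixed-effects model analysis makes the time-by-group interaction terms the main findings of a confirmatory analysis but names no directional test. The nearest the article comes is the hypothesis under Anticipated Findings: "We hypothesize that participating in a visual arts intervention will be associated with improvements in psychological adjustment, self-concept, and HRQoL". That gives an expected direction and does not define a test.

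**The concern.** An α of .05 with no qualifier is ordinarily read as two-sided, and a group effect from a mixed model is by convention reported with a two-sided p value and a 95% interval. On that reading the listed inputs do not lead to 156.

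Two things are at stake. First, a null result would be presented as coming from a study with a 10% chance of missing an effect of d = 0.5, when the two-sided chance is nearly 17% even if the children are treated as independent. Second, leaving the sidedness open leaves the confirmatory threshold open: a one-sided p of .04 is .08 two-sided. The article says that data collection is complete, so this choice should not be left until the group comparison is known.

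**Working it through.** **Inputs, all from the Participants section:** d = 0.5 (so SD = 1), α = .05, power 90%, two independent means, 2:1 allocation, 30% loss. Sidedness is not given, so both versions are run.

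**1. Reproducing the plan's figure (normal approximation).** With *n* controls and 2*n* intervention children,

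*n* = (z_α + z_power)² × (1 + 1/2) / d², with z_power = 1.2816.

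- One-sided, z_α = 1.6449: *n* = (2.9264)² × 1.5 / 0.25 = 51.4, rounded up to 52. Total 52 + 104 = **156**, the stated figure in total and in each arm.
- Two-sided, z_α = 1.9600: *n* = (3.2415)² × 1.5 / 0.25 = 63.0 (63.04 before rounding), rounded up to 64. Total 64 + 128 = **192**.

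**2. Exact check (noncentral t).** For 104 and 52, df = 154 and the noncentrality is 0.5 × √(104 × 52 / 156) = 2.944.

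| Test at α = .05 | Critical t | Power at 104/52 | Smallest 2:1 design with 90% power |
|---|---|---|---|
| One-sided | 1.655 | 90.1% | 104 + 52 = 156 |
| Two-sided | 1.975 | 83.3% | 128 + 64 = 192 |

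The one-sided match is tight: 102 + 51 gives 89.6%, just short of 90%. The normal approximation puts power at 104/52 at 90.3% one-sided and 83.7% two-sided, so the gap does not come from the choice of approximation.

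**3. Other routes to 156.** Equal allocation gives 170 (normal) or 172 (t) two-sided, and 138 or 140 one-sided. Dividing the 2:1 totals by a rank-test efficiency of 3/π or 0.864 gives about 163 to 181 one-sided and 201 to 222 two-sided. None gives 156. A two-sided test at α = .10 would, but it is the same calculation as one-sided .05 and is not what the article states.

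**4. Allowance for loss.** 156 / 0.70 = 222.9, rounded up to 223, which reproduces. The two-sided equivalent is 192 / 0.70 = 274.3, rounded up to 275.

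**5. Detectable effect.** With 104 and 52 at two-sided .05 and 90% power: (1.9600 + 1.2816) × √(1/52 + 1/104) = 3.2415 × 0.1698 = 0.55 (0.554 by noncentral t).

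**6. Does the reported enrolment close the gap?** The Results section reports 179 enrolled. Assuming a 2:1 split, which is not stated for those 179, two-sided power for d = 0.5 is about 88% with no loss at all. After the plan's own 30% loss (179 × 0.70 = 125.3, about 126 children), it is about 75%.

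**The case against.** The strongest reply is that nothing has been miscalculated. With a one-sided α of .05 the figure of 156 is exactly right, the step to 223 follows, and the article never says two-sided. The hypothesis is worded as an improvement, which suits a one-sided test. The article is condensed, and the sidedness of the confirmatory test may be set in a full protocol or analysis plan that is not shown.

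The arithmetic part stands: the fault is an undeclared one-sided α, not a slip in computation. The rest does not remove the problem. Trials commonly state an expected direction and test two-sided, so the hypothesis does not settle the test. The sample size is not a detail left for later either: the article publishes a complete calculation, and its 90% is wrong under the ordinary reading of its inputs. A later document could declare a one-sided test, but it could not make 90% the power of a two-sided one.

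A second reply is that 83.3% is not the power of the planned analysis, which is an adjusted mixed model using both assessments and a random cluster intercept. This is correct. Ignoring clustering, a correlation between baseline and post-intervention scores above about 0.43 (baseline-adjusted analysis) or about 0.59 (change-type contrast) would bring two-sided power at 104/52 to at least 90%. The article gives no such correlation, and clustering works in the other direction. Neither adjustment enters the article's own calculation, so the fair comparison is like with like: the same simple t test, one-sided against two-sided.

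Finally, recruitment is over, and no estimate or interval changes. That limits the remedy to wording, but it does not make the published figure right.

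**Conclusion.** The concern holds. Of the standard variants tried, only a one-sided α of .05 reproduces 156 as 104 + 52, and the article declares no one-sided test. For a two-sided test at .05 and d = 0.5, power with 104 and 52 children is 83.3%, which is 6.8 points below the one-sided 90.1%. The type II error is 16.7% against a stated 10%. Two-sided 90% power would need 192 children completing (275 recruited at 30% loss), against 156 and 223. The effect detectable with 90% power is about 0.55.

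These figures rest on the article's own framework: an unadjusted comparison of two means in independent children, with d = 0.5 and 2:1 allocation. They include neither a gain from baseline adjustment nor a loss from clustering. If a one-sided test was always intended, the number is right and the defect is that the test is not declared.

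**What to change.** Choose one of two corrections, and date it relative to the outcome analysis:

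- **Two-sided test.** Restate the calculation along these lines: with two-sided α = .05, 156 children (104:52) give 83% power for d = 0.5, or 90% power for d of about 0.55, before any allowance for clustering.
- **One-sided test, if that was always the intention.** Say so in the Participants section and in the mixed-effects analysis section, give the reason, and report the confirmatory test as one-sided at .05.

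Do not enrol more children; recruitment and data collection are finished, and only the stated figure or the declared test needs to change. The cost is wording and, on the two-sided route, a less favourable power figure.
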